**Participant timeline**

Clusters will be enrolled and randomized to trial arms in June 1, 2022. Baseline recruitment and interviewing of women within study clusters began in June 5, 2022 and will be completed after four months of intervention.

**Intervention fidelity**

Fidelity of the intervention will be maintained based on the National Institutes of Health Behavioural Change Consortium developed best practice recommendations (Bellg et al., 2004). The intervention design has conceptual framework. Non adjacent clusters will be selected to prevent information contamination. Equal numbers of clusters will be taken for the intervention and control groups from each district to balance variations. The intervention process will be pretested before the implementation of the trial. Each pregnant mother will receive equal numbers and frequencies of training, and the lengths of contacts within an intervention group will be similar to make the process standardized. Group education training will be given in a group using a training manual, role-playing, and mock counselling practice. The competency of recruited religious leaders will be monitored by pre-post training test. The test focuses on knowledge and attitudes towards intervention key messages. If the post-training test score of the trained religious leaders is below acceptable range, retraining will be given on identified gaps of intervention messages. Training sessions will be randomly selected for process evaluation and all selected sessions will be evaluated by one process evaluator. The process observer rated the educator using a ‘yes/no’ rating system on items such as using a training guide, provision of the whole content, duration and frequency of training, preparedness, accuracy, and ability to properly respond to questions. Intervention receipt will be assessed using checklists on knowledge of the pregnant mothers on maternal health behaviour through interviewing about their understanding of the core contents of the intervention. Intervention enactment will be assessed on utilizations of antenatal care and skilled delivery.

Routes of **persuasive message**

*Central route:* The ability of a person to comprehend information depends on the quality of the information which can be described into two elements: information completeness and information accuracy(Chang et al., 2020, Filieri and McLeay, 2014). This study adopted both elements as central route factors. Information completeness is referred to when there is sufficient depth and breadth of information in communication (Chang et al., 2020). Information accuracy for this study is defined as the degree to which information is correct, accurate, and unambiguous (Chang et al., 2020, Lee et al., 2002). Accurate information needs to show interrelation and consistency between provided data and reality (Thoroddsen et al., 2013). In the context of maternal health education through religious leaders, information accuracy requires all the discussed information to be accurate and consistent. Scholars argue that to increase the effectiveness and accuracy of information, attention needs to be given to the source of communication.

***Peripheral Route:*** According to the elaboration of likelihood model, besides argument quality representing the central route in influencing attitude, the peripheral route is best explained by other “cues” that affect the individual attitude through bypassing the argument processing (Petty and Cacioppo, 1986). Scholars argue that the cue is operative when the individual is being “unmotivated by the subjects or is unable to process the issue-relevant arguments”, abundantly found in the central route (Petty and Cacioppo, 1986). Therefore, the individual looks for simpler cues, such as source credibility, aesthetics, and popularity (Chang et al., 2020). In this study, these peripheral routes of persuasion of maternal health education messages will be considered during the recruitment of the religious leaders.

**4.16 Measurements and indicators**

Trained interviewers will conduct face-to-face interviews using structured questionnaires. Questionnaires contain sections on socio-demographics, Reproductive history of respondent, maternal health service utilization, birth preparedness and complication readiness, knowledge of danger signs during pregnancy, labor and child birth, new-born and postpartum period, perception about pregnancy, childbirth, and the period immediately after childbirth, attitude towards safe delivery utilization and religious leaders’ engagement scale measurement tool. Antenatal care service utilization will be measured based on “at least one ANC attendance” (Women who have attended at least one ANC check-up during their current pregnancy) and “four or more ANC attendance” (Women who attended four or more ANC visits) during their current pregnancy as reported by the participant. Skilled delivery service utilization will be measured based on women who gave birth in health center and hospital by assistance of health professionals that have midwifery skills including Midwife nurse, Nurse, Health Officers and Doctors *as* reported by the participant.

Knowledge of danger signs during pregnancy has 14 items, Knowledge of danger signs of labor and childbirth has 9 items and knowledge of neonatal danger signs has 11 items. All Knowledge score will be computed by adding the total number of correct spontaneous responses to maximum number of items with a minimum score of 0 and maximum of number of items (0 when a mother mentioned none of the key danger signs and maximum number when the mother mentioned all the danger signs). Spontaneous response is respondents’ naming of danger signs without giving option of the respective signs. Accordingly, two categories will be developed for knowledge of danger signs (Good and poor categories). Women who mention at least three neonatal danger signs will be considered to have good knowledge whereas those who mentioned less than three of the danger signs will be labelled to have poor knowledge as stated by several studies. Questionnaire on BPCR is adopted and modified from monitoring BPCR tools for maternal and new-born health (Maternal, 2004). Attitude towards skilled delivery service utilization has 12 items that will be measured by using Likert scale where respondents are supposed to strongly agree, agree, neutral, disagree and strongly disagree. The overall attitude score will computed by summing up the items after performing the reverse scoring for negatively worded sentences. A higher composite score indicated a more favourable attitude.

*Perception of Pregnancy Risk Questionnaire (PPRQ****)*** was developed by Heaman and Gopton (Heaman and Gupton, 2009). It is a self-report questionnaire consisting of 9 visual analogue scales designed to measure a pregnant woman’s perception of her pregnancy risks. This questionnaire consists of two subscales that include four questions about the risk to self (mother), (for example “is a risk of having a cesarean section”); and five questions about risk to the baby, (for example “is a risk of baby having a birth defect”). “Respondents will be asked to put a vertical mark through the line to indicate their assessment of risk for each Item,” (yielding a score ranging from 0-100). A total PPRQ score will be obtained by adding the score for each of the 9 items, and then dividing by 9, to obtain a score out of 100. Higher scores will indicate higher levels of perceived risk.

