**The focuses of training (intervention key messages) on:**

**Antenatal care:** (taking TT injection, taking Calcium Consumed 100+ IFA tablets , eating more food during pregnancy, eating Green vegetables , eating Fruits during pregnancy , drinking milk during pregnancy , eating pulses and beans during pregnancy , taking nap/rest, regularly during pregnancy, Husband accompanying for ANC (regularly /mostly), Human immunodeficiency virus (**HIV)**  **and syphilis** test, tobacco use and substance use. **Benefits of early and exclusive breastfeeding (**Provides the best nutrition for the new-born Is easily digested and efficiently used by the baby’s body, Protects against infection and other illnesses, Offers some protection against allergies, Is cost-effective and affordable, Promotes mother-baby bonding. **Unhealthy beliefs and practices about feeding new-borns**, **Hygiene during pregnancy**, **Breastfeeding and contraception, Benefits of birth spacing: (**Maternal mortality, fetal death (miscarriage or stillbirth), neonatal mortality, Anaemia in the mother during subsequent pregnancies, Postpartum inflammation of the endometrium lining the uterus, Premature rupture of the amniotic membranes surrounding the fetus, Premature birth, Intrauterine growth retardation and a low birth-weight baby and Malnutrition of new-borns and infants due to insufficient breast-milk**).**

**Prenatal Danger signs: (**Severe headache, Blurred vision, Fatal movement absent, High blood pressure, Edema of the face/swelling, Oedema of the hands/leg swelling, Convulsions, Excessive vaginal bleeding, Severe lower abdominal pain and Leaking fluid (meconium stained).

**Labor/delivery** **Danger signs: (**Excessive vaginal bleeding, Foul-smelling discharge, High fever, Baby’s hand or feet coming out first, Baby is in abnormal position, Prolong labor (.12 hours), Retained placenta, Rupture uterus, Cord prolapse, Cord around neck and Convulsion).

**Postpartum Danger signs:** (Excessive vaginal bleeding**,** Foul-smelling discharge**,** High fever**,** Inverted nipples**,** Tetanus**,** Retained placenta**,** severe abdominal pain**,** Convulsions **and** Engorged breasts/swelling of breasts)

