**Neonatal Danger signs: (**Poor feeding or unable to suck**,** Diarrheal**,** Redness around the cord**,** Red eye/discharging eyes**,** Difficult breathing**,** Yellow coloration of the skin/jaundice**,** Hypothermia/shivering**,** Blisters on skin/Skin lesion**,** Baby doesn’t cry**,** Fever**,** Unconscious**,** Fast breathing**,** Chest in drawing**,** Doesn’t pass urine**,** Doesn’t pass stool and Convulsions.

**Consulting doctor or others health professionals:** if they have danger signs (during pregnancy, labor and childbirth, 42 days after delivery, and neonatal danger signs).

**Birth preparedness and complication readiness:** (plan for where to give birth, plan for a skilled birth attendant, plan to save money, plan for transportation and identification of compatible blood donors in case of emergency).

**Delivery at a health facility with a skilled provider** and **postnatal care:** (Women discuss FP method with husband Women adopted FP method after delivery Mother fed colostrum to the baby).

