**Part V Knowledge of obstetric danger signs**

| **Sir. No.** | **Questions** | | **Responses** | **Skip to** |
| --- | --- | --- | --- | --- |
| 501 | In your opinion, can unforeseen problems related to pregnancy occur during any pregnancy or childbirth that could endanger the life of a woman? | | 1. Yes 2. No 3. I don’t know |  |
| 502 | In your opinion, what are some serious | | 1. Bleeding , 1. Yes, 2. No 2. Severe headache, 1. Yes, 2. No 3. Blurred vision,1. Yes, 2. No 4. Convulsions, 1. Yes, 2. No 5. Swollen hands/face, 1. Yes, 2. No 6. High fever, 1. Yes, 2. No 7. Loss of consciousness, 1. Yes, 2. No 8. Difficulty breathing, 1. Yes, 2. No 9. Severe weakness , 1. Yes, 2. No 10. Severe abdominal pain, 1. Yes, 2. No 11. Accelerated/ reduced, 1. Yes, 2. No 12. Fetal movement, 1. Yes, 2. No 13. Water breaks without labor, 1. Yes, 2. No 14. other specify 15. None 16. I don’t know |  |
| 503 | In your opinion, what are some serious health problems that can occur during labor and childbirth that could endanger the life of a pregnant woman?  PROBE: Any others? | | 1. Severe bleeding, 1. Yes, 2. no 2. Severe headache, 1. Yes, 2. no 3. Convulsions, 1. Yes, 2. no 4. High fever, 1. Yes, 2. no 5. Loss of consciousness, 1. Yes, 2. no 6. Labor lasting >12 hours, 1. Yes, 2. no 7. Placenta not delivered 30 minutes after baby, 1. Yes, 2. no 8. other___ (specify) 9. none 10. don’t know |  |
| 504 | In your opinion, could a woman die from [this problem] any of these problems? | 1. Yes 2. No | |  |
| 505 | In your opinion, what are some serious health problems that can occur during the first 2 days after birth that could endanger the life of the woman?  PROBE: Any others? | 1. Difficult or fast breathing, 1. Yes, 2. No 2. Yellow skin/eye color (jaundice), 1. Yes, 2. No 3. Poor sucking or feeding, 1. Yes, 2. No 4. Pus, bleeding, or discharge from around the umbilical cord, 1. Yes, 2. No 5. Baby very small, 1. Yes, 2. No 6. Skin lesions or blisters, 1. Yes, 2. No 7. Convulsions/spasms/ rigidity, 1. Yes, 2. No 8. Lethargy/ unconsciousness, 1. Yes, 2. No 9. Red or swollen eyes with pus, 1. Yes, 2. No 10. other (specify)____________ 11. none | |  |
| **506** | In your opinion, could a newborn baby die from [this problem] any of these  Problems? | 1. Yes 2. No 3. I don’t know | |  |

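### Six of 11 taught labour signs and 7 of 16 taught neonatal signs have no named answer code, and the stated item totals imply at most one point for everything written under 'other'

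*Protocol*

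**What the plan says.** Section 4.16 defines the knowledge scores: "All Knowledge score will be computed by adding the total number of correct spontaneous responses to maximum number of items". The same sentence sets the minimum at 0, so the rule reads as a count of correct unprompted answers, up to the number of items. The totals for the first two scores read "Knowledge of danger signs during pregnancy has 14 items, Knowledge of danger signs of labor and childbirth has 9 items". The neonatal score gets a total of 11. The cut is "Women who mention at least three neonatal danger signs will be considered to have good knowledge"; the operational definition in section 4.18 repeats it, also worded for neonatal signs only.

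The key messages in section 4.13 fix what is taught: 10 pregnancy, 11 labour and 16 neonatal signs. The labour list ends with "Retained placenta, Rupture uterus, Cord prolapse, Cord around neck and Convulsion". The neonatal list includes "Chest in drawing".

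Annex 1, Part V fixes what can be ticked. Q503 (labour) has seven named signs, ending "Placenta not delivered 30 minutes after baby, 1. Yes, 2. no 8. other___ (specify". Q505 has nine named newborn signs, among them "Baby very small, 1. Yes, 2. No 6. Skin lesions or blisters", then a single 'other (specify)' line and 'none'. No passage says how text written under 'other' is scored.

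**The concern.** Objective 1 asks whether the teaching improves knowledge of danger signs in pregnancy and childbirth, and the Hypothesis adds neonatal signs. If the form names only part of the curriculum and the remainder shares one line worth at most one point, correct recall of taught material is partly discarded. Only the intervention arm receives that teaching, so the lost credit should fall mainly there. The between-arm difference in the proportion with good knowledge would then be pulled towards zero. The form also names signs that are absent from the matching taught list (severe headache and loss of consciousness in labour, a very small baby), and these earn a point in either arm.

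**Working it through.** **1. Reproduce the stated item totals from Annex 1, Part V.**

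| Score | Named signs | + 'other' + 'none' | Stated in 4.16 |
|---|---|---|---|
| Pregnancy (Q502) | 12 | 14 | 14 |
| Labour (Q503) | 7 | 9 | 9 |
| Neonatal (Q505) | 9 | 11 | 11 |

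The 12 treats the two printed lines on fetal movement as one sign, as the Amharic form does. Named signs alone (12, 7, 9) do not give the stated totals. The totals therefore count 'other' as one item, and 'none', which is not a danger sign, as another.

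**2. Match each taught sign (section 4.13) to a named code.**

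| List | Taught | With a named code | Without |
|---|---|---|---|
| Pregnancy | 10 | 9 | 1: high blood pressure |
| Labour | 11 | 5 | 6: foul discharge, hand or feet first, abnormal position, uterine rupture, cord prolapse, cord round neck |
| Neonatal | 16 | 9, in 8 codes | 7: diarrhoea, hypothermia, no cry, fever, chest indrawing, no urine, no stool |

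Difficult and fast breathing share one Q505 code. Redness round the cord is matched to the cord pus/discharge code; a strict reading would leave 8 neonatal signs without a code.

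**3. A case needing no assumption about recall.** A woman names newborn fever, hypothermia and chest indrawing, all taught. She gets 0 named codes, or 1 point if 'other' is one item. Either is below three, so she is classed as poor.

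**4. Illustration: any three of the 16 neonatal signs, all sets equally likely (assumed).** Number of sets: C(16,3) = 560.

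- Named codes only: C(9,3) − 7 = 84 − 7 = 77 (the 7 contain both breathing signs). 77/560 = 13.8% good.
- 'Other' worth at most one point: add two distinct codes plus one uncoded sign, (C(9,2) − 1) × 7 = 35 × 7 = 245. (77 + 245)/560 = 322/560 = 57.5% good.
- Each correct 'other' entry credited: only the 14 sets holding both breathing signs can still fall short, 546/560 = 97.5%. With that code split, 560/560 = 100%.
- Strict cord matching lowers the first two to 50/560 = 8.9% and 266/560 = 47.5%.

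**5. More signs recalled (named codes only / 'other' capped at one).** Four signs: 665/1820 = 36.5% / 1449/1820 = 79.6%. Five signs: 2625/4368 = 60.1% / 3997/4368 = 91.5%.

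**6. Labour, if the same cut of three were applied.** Three of 11: C(5,3)/C(11,3) = 10/165 = 6.1% on named codes; (10 + C(5,2) × 6)/165 = 70/165 = 42.4% with 'other' capped at one.

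**7. Pregnancy, same cut, for contrast.** Three of 10 with 'other' capped at one: 112/120 = 93.3% good.

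**8. Whole-list recall.** This reaches 8 pregnancy, 5 labour and 8 neonatal named codes (7 on strict matching). All are above three.

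**The case against.** The best defence is that nothing is lost. Both questions have an 'other (specify)' line, so every taught sign can be recorded. Section 4.16 speaks of correct spontaneous responses and of signs mentioned, not of pre-printed codes. Read literally, three correct 'other' entries score three, and detailed back-coding rules often sit outside a protocol. That stands in part: a reader might infer that these signs cannot be recorded at all, and the form does not support that. The one-point cap is an inference from the item totals, not a stated rule. But totals of 9 and 11 fit only if 'other' is one item, so the protocol's own figures point away from the generous reading. That is a mismatch within this document, not a detail left for later.

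A reader might also infer that a woman who recalls everything she was taught is scored as poor. She is not (step 8). Nor is the gap uniform, since 9 of 10 pregnancy signs are named.

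Equal recall is doubtful. Most of the major danger signs listed in section 2.4 that are also on the taught labour list have a code in Q503; foul discharge is the exception. If those are the signs women remember best, the loss is smaller than shown.

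Finally, the sample size rests on skilled delivery (section 4.8), and section 4.7.1 lists knowledge among the independent variables. That limits the weight of the point but does not remove it, because knowledge is the stated outcome of Objective 1.

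**Conclusion.** The point holds for partial recall of labour and neonatal signs. Taught list, form and item totals do not fit together, and a woman who correctly names three taught signs can fall below the cut. The counts (6 of 11 and 7 of 16 without a named code) come straight from the protocol. The percentages are illustrative. They rest on equally likely recall sets and on how 'other' is credited: for three neonatal signs, 13.8% good on named codes only, 57.5% with 'other' capped at one point, and 97.5% to 100% if each entry is credited. The capped figure best fits the stated totals. The labour figures also extend a cut that is worded for neonatal signs only.

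Dilution mainly in the intervention arm is the expected direction. Its size cannot be computed, because the protocol gives no recall rates. It would be wrong to conclude that correct recall is bound to be lost, or that the pregnancy score is materially affected.

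The neonatal figures further assume that women answer Q505 with newborn signs, although its stem asks about danger to the woman.

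**What to change.** Before data collection:

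- Add named codes for the taught signs that lack one, six in Q503 and seven in Q505, and split difficult from fast breathing, in the English and Amharic forms alike.
- State in section 4.16 that every distinct correct sign scores one point, whether ticked or written under 'other'. Have 'other' text back-coded blind to arm against a pre-set list that includes correct signs not taught. Crediting only curriculum-matched codes would favour the intervention arm.
- Restate the maxima so that 'none' and 'other' are not items. Named signs would number 7 + 6 = 13 for labour and 9 + 7 + 1 = 17 for neonatal; the maximum is the length of the pre-set list.
- Reconcile the Q505 stem with its newborn answer codes; without this the neonatal score does not work whatever codes are added.

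The cost is 13 extra answer codes, one split code and some back-coding. Interview time hardly changes because answers are unprompted. The score will no longer be identical to the source tool. If baseline interviews have already been done on the present form, the recorded 'other' text can be back-coded under the same rule, so that both survey rounds are scored alike.

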# Summary

Background: Despite the many supply- and demand-side interventions aimed at increasing uptake of maternal health service utilizations, the maternal and new-born health service utilizations remains low. Religious leaders have the power to inhibit or facilitate effective adoption of maternal health service utilizations to promote maternal and child health. However, evidence on the roles of religious leaders in promoting maternal health behaviour in developing world is not fully known. Therefore this cluster-randomized trial is designed to evaluate the effects of trained religious leaders’ engagement in maternal health service utilizations and knowledge of major obstetric danger signs.

Methods: A community based cluster randomized control trial in which the study kebeles are randomly assigned into intervention and control groups will be conducted. The sample size is calculated using stata software. Three hundred six pregnant mothers will be enrolled in each group. The intervention comprised of the messages on maternal health and new-born care by trained religious leaders. A baseline study will be conducted before the intervention and post-intervention evaluation will be conducted after four months. Religious leaders will be selected and trained to lead participatory sessions on maternal health and new-born care. Data on maternal health service utilizations, knowledge about obstetric danger signs, attitude towards skilled delivery service utilization and perception of pregnancy risk will be collected from a repeated cross sectional household survey. Effect of intervention will be assessed using multivariable logistic regression with generalized estimating equation model. Mixed-effects multilevel logistic regression model will be used to identify determinants of skilled delivery service utilizations. Data will be analyzed using STATA software. For qualitative study, coded transcripts will be further analyzed and summarized in narratives for each theme and sub-theme.

**Work plan and budget:** the project will take about one year for completion and the total estimated cost is 256,000 Birr.

**Key words:** Religious leaders, maternal health, Hadiya Zone

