## 4.8 Sample size

In accordance with the main objective of the larger study, the sample size estimate is designed to detect changes in the proportion of skilled delivery service utilization. The sample size is calculated using stata software based on the following assumptions. Tail (s): One; effect size (d): 0.15; **α** error probability = 0.05; power (1-**β** error probability) = 0.8, and allocation ratio (N1/N2) = 1. This gives a sample size of 155. Then, adding design effect, DE = 1+(m-1)ICC , where m=Average cluster size, m= 50, ICC=0.02 based on a published study ICC (Killip et al., 2004), DE=2, and allowing for a 10% loss to follow up, the total sample size is 682 (N1 = 341 and N2 = 341). N1 and N2 are sample sizes in the control and intervention group, respectively. Based on these assumptions, the estimated sample size is: 306 pregnant mothers per group to detect a 15-percentage point anticipated difference in the proportion of skilled delivery service utilization (an increase from 26% to 41%). This estimate is based on the baseline skilled delivery service utilization in the Ethiopia Demographic and Health Survey (26% from EDHS 2016, SNNP region report) in the control group (CSA, 2016).

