**Knowledge of obstetric danger signs**

Women who mention at least three neonatal danger signs will be considered to have good knowledge whereas those who mentioned less than three of the danger signs will be labelled to have poor knowledge as stated by several studies.

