## 4.19 Statistical analysis

Data of baseline and end-line surveys will be combined and analyzed using Stata 14.1. Analyses will be based on the intention-to-treat principle and compared differences of the outcomes between the intervention and control at both individual and cluster levels. First, Univariate analyses will be performed to explore the characteristics of respondents. We then will use logistic regression with random effects to estimate the effect of the intervention on prenatal behaviour, adjusting for clustering. Generalized estimated equations (GEE) regression analyses adjusted for clustering will be used to test the effect of the intervention on promoting maternal health behaviour. We will repeat analyses for the primary and secondary outcomes adjusted for baseline differences by fitting an interaction term between study period (baseline vs intervention) and allocation in each model. Mixed-effects multilevel logistic regression model will be used to identify determinants of birth preparedness and complication readiness.

**For qualitative study:** The interviews will be recorded and transcribed verbatim. The transcripts will be thematically analyzed using the qualitative software program Atlas.ti 6.0. Two analysts will independently code the transcripts and subsequently review, discuss, and refine the coding schemes until consensus will be reached. Emerging concepts will be assessed using the constant comparative method from grounded theory. This means that when this concept will be identified, previously analyzed interviews will be reviewed in order to check if their content fitted into this concept. A final version of the code book will be then developed leading to identification of themes, and sub-themes. Coded transcripts will be further analyzed and summarized in narratives for each theme and sub-theme. Study findings will be presented, discussed, and validated in a stakeholder meetings conducted in regional and district health offices.

| S.no | Research objectives | Study populations | Study design | Data source | Major outcome variables | Analytic model |
| --- | --- | --- | --- | --- | --- | --- |

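### Danger-sign knowledge is scored as a count, then reduced to good or poor, and no analysis of the count is named for Objective 1

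*Protocol*

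**What the plan says.** Objective 1 (section 3.2 and Table 4) concerns the effect of the intervention on knowledge of danger signs in pregnancy and childbirth. Section 4.16 builds a score for each domain by adding correct spontaneous answers, with 14 items for pregnancy, 9 for labour and childbirth and 11 for the newborn. It continues: "Accordingly, two categories will be developed for knowledge of danger signs (Good and poor categories". The category is then defined only as naming at least three neonatal signs.

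The operational definition headed Knowledge of obstetric danger signs repeats that cut and gives nothing else: "those who mentioned less than three of the danger signs will be labelled to have poor knowledge as stated by several studies".

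On the model, the Summary states: "Effect of intervention will be assessed using multivariable logistic regression with generalized estimating equation model". Section 4.19 says: "We then will use logistic regression with random effects to estimate the effect of the intervention on prenatal behaviour, adjusting for clustering". It then adds a cluster-adjusted GEE without naming a link. The Objective 1 row of Table 4 says only GEE regression. No section names an analysis of the summed score.

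The sample size in section 4.8 is for skilled delivery, not knowledge.

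**The concern.** The protocol already produces a graded measure and then discards most of the grading. Section 4.13 lists 10 prenatal, 11 labour/delivery and 16 neonatal signs to be taught, so improvement can be expected along the whole count. Under a three-sign cut, a woman who goes from 0 to 2 signs or from 3 to 9 contributes nothing to the effect, and the result depends on where women in these kebeles happen to sit relative to three. With six clusters per arm, information is scarce. What is at stake is a higher chance of missing a real effect on a stated objective, for no saving in data collection.

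**Working it through.** **Inputs from section 4.8.** 26% vs 41% (skilled delivery), alpha 0.05, power 0.80, 1:1 allocation, m = 50, ICC = 0.02, 306 per group. There are six clusters per arm (Randomization section).

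**The plan's own figure.** n = [z_a·√(2p̄(1−p̄)) + z_b·√(p0(1−p0) + p1(1−p1))]² / (p1−p0)², with p̄ = 0.335. Two-sided this gives 154.2, so 155 as stated; 155 × 1.98 = 306.9 and 155 × 2 × 1.10 = 341. One-sided it gives 122, so the stated "Tail (s): One; effect size (d): 0.15" does not match 155. That is a separate matter; both sidednesses are shown below.

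**Assumptions, because the protocol has no figures for knowledge.** The 26% to 41% contrast is borrowed for the share naming at least three signs. The whole distribution shifts, counts are Poisson, and the arms are compared at end line only.

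**Effective size.** Design effect = 1 + 49 × 0.02 = 1.98; 306/1.98 = 154.5 per arm.

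**Cut at three.** z = 0.15/√((0.26×0.74 + 0.41×0.59)/154.5) = 2.83.

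**Count.** Poisson means giving 26% and 41% at three or more are 1.765 and 2.323. z = 0.558/√((1.765 + 2.323)/154.5) = 3.43.

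Power with equal ICC of 0.02:

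| Test | Cut | Count | Loss (points) |
| --- | --- | --- | --- |
| One-sided, normal | 88.2% | 96.3% | 8 |
| One-sided, t on 10 df | 83.8% | 93.8% | 10 |
| Two-sided, normal | 80.8% | 92.9% | 12 |
| Two-sided, t on 10 df | 72.3% | 87.0% | 15 |

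Negative binomial counts (size 1, 2, 4) give 92.9 to 93.6% for the two-sided normal case, so the Poisson form is not what drives the result. With equal ICC, other starting levels (from 10 to 25% up to 60 to 75%) give losses of about 3 to 20 points.

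**Unequal ICC.** A score often carries a higher ICC than its dichotomy. The same formulas, with separate design effects:

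| ICC cut / count | Effective n cut / count | One-sided normal | Two-sided normal | Two-sided t, 10 df |
| --- | --- | --- | --- | --- |
| 0.015 / 0.022 | 176.4 / 147.3 | 91.6 vs 95.6% | 85.6 vs 91.8% | 77.8 vs 85.4% |
| 0.02 / 0.03 | 154.5 / 123.9 | 88.2 vs 92.3% | 80.8 vs 86.7% | 72.3 vs 79.0% |
| 0.02 / 0.04 | 154.5 / 103.4 | 88.2 vs 87.7% | 80.8 vs 80.1% | 72.3 vs 71.6% |

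The gain is 4 to 8 points in the first two rows and nil in the third. A simulation with bounded 9-, 11- and 14-item counts, 6 clusters of 51 per arm and ICCs near 0.015 and 0.022 agrees with the first row: 75 to 77% for the cut, 82 to 85% for the score.

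**Effect concentrated at the cut.** If 15 percentage points of women move from two signs to three and nobody else changes, the mean rises by 0.15. Then z = 0.15/√((1.765 + 1.963)/154.5) = 0.97, and power for the count is 16% two-sided or 25% one-sided, against about 80% and 88% for the cut.

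**The case against.** Several points on the other side are fair.

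- The Objective 1 row names neither a link nor a category. The logistic sentence in 4.19 concerns prenatal behaviour, so logistic for this outcome rests on the general sentence in the Summary. A SAP, which is not shown, could choose the score. This stands as a limit on certainty. Even so, the protocol itself fixes the two categories and makes a category the whole operational definition, and a good/poor outcome is binary under any GEE.
- A reader might infer that Objective 1's own counts are expressly cut at three. The text does not say so: the cut is worded for neonatal signs, while Objective 1 concerns pregnancy and childbirth. Applying it there is an inference, and the mismatch needs correcting in its own right.
- At the borrowed contrast the cut still has about 81% power (two-sided normal), which meets the 80% used for sizing. Section 4.7 lists knowledge among the independent variables, not the dependent ones. That limits the consequence, but Objective 1, the Hypothesis and Table 4 all treat knowledge as an outcome to be tested.
- At least three signs is easy to interpret and is said to follow earlier studies. That is a reason to report it, not a reason to leave the count untested.
- A mean count is exposed to unclear item lists. Section 4.16 says 14 pregnancy and 9 labour items. The English questionnaire prints 13 named pregnancy signs, with fetal movement split from its qualifier, and 7 labour signs; the Amharic version prints 12 pregnancy signs. This stands, and the fix has to deal with it.

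**Conclusion.** The point holds as an inexpensive improvement. The protocol computes a count, reduces it to two categories and names no analysis of the count, so changes that do not cross the cut are lost.

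The size is conditional. With a borrowed 26% to 41% contrast, a whole-distribution shift, 306 per arm and equal ICC of 0.02, the cut costs roughly 8 to 15 points of power. The cost is about 4 to 8 points if the score's ICC is moderately higher and nil if it is double, and the order reverses if the effect only moves women from two signs to three. Nothing in the session content targets that single step, which makes the reversal less likely but does not exclude it.

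A reader might infer that a fixed loss of power is built into the trial, or that the loss exceeds five points whatever is assumed. The documents support neither: they contain no figure for knowledge, and the unequal-ICC and concentrated-effect cases contradict the second.

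**What to change.** In section 4.16, the operational definition, section 4.19 and the Objective 1 row of Table 4:

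1. Make the summed number of correctly named pregnancy and labour/childbirth signs the outcome tested for Objective 1. State whether each domain is tested or a combined score.
2. Analyse it by cluster-adjusted GEE with an identity or log link and a small-sample correction suited to 12 clusters. Report the difference or ratio in mean number of signs.
3. Align the item counts in 4.16 with the English and Amharic questionnaires, so that the score has one defined range.
4. Keep at least three signs as a secondary proportion, and state which domain it refers to.

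The cost is wording and an item-list check. No visits or participants are added, and the score is already to be computed. The downside is that a difference in mean number of signs is less directly comparable with studies reporting good knowledge; the secondary proportion covers that.
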